**Methods:**

A total of 45 people with PD, between 35 and 85 years old and Hoehn and Yahr stages between I to III, will be recruited from movement disorder centers for this three-armed study. Participants will be randomized into three groups (occupation-based interventions with responsibility feedback, occupation-based interventions without responsibility feedback, and conventional interventions). All participants will receive intervention for 24 sessions during a period of 12 weeks (2 sessions per week). The primary outcome measure will be participation satisfaction. Participation frequency and restriction, self-perceived performance, performance satisfaction, motivation, volition, sense of agency, responsibility, physical activity, community integration, activities of daily living (ADL), instrumental ADL, upper extremity function, balance, fatigue, and quality of life will be measured as secondary outcome measures. All outcomes will be measured at baseline, session 9, session 17, post-intervention (week 13), and follow-up (week 25).

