### Primary outcome measure

The primary outcome of this trial will be participation satisfaction assessed with the Utrecht Scale for Evaluation of Rehabilitation-Participation Satisfaction Scale (USER-P). The satisfaction scale consists of 10 items including vocational activities, leisure activities, and social relationships. Each item will be rated on a 5-point Likert scale. The summation of scores will be converted to a 0–100 scale, with higher scores indicating greater participation satisfaction [54]. The Persian version of the USER scale has shown appropriate validity and reliability [55].

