*Allocation of Treatment Responsibility Scale* will evaluate the responsibility during medication-related tasks for caregivers and patients with two parallel forms. Each item is rated from 1 (none of the time) to 4 (all the time). The total score will be the summation of items, with higher scores reflecting increased perceived responsibility [60].

Physical activity

*Phone Frequency, Intensity, Time, and Type (Phone-FITT) Questionnaire* will measure the physical activity participation in household (6 items) and recreational (11 items) activities. The frequency and duration of each activity will be asked. The duration is rated on a 4-point scale (0 = 0 min; 1 = 1–15 min; 2 = 16–30 min; 3 = 31–60 min; 4 = 1 h and more). Higher scores will indicate greater levels of physical activity participation [61].

Community integration

*Community Integration Questionnaire-Revised* will evaluate the individual’s integration into home and community with 18 items. Most items will be rated on a scale of 0 to 2, with 2 representing greater integration. Subscale scores will be calculated as follows: home integration (0–12), social integration (0–10), productivity (0–7), and electronic social networking (0–6). Higher scores will reflect a higher degree of community integration [62].

ADL and IADL

*Nottingham Extended ADL Scale* will be used to assess the level of independence in mobility, kitchen, domestic, and leisure activities. Each item will be scored with 4 (no (0 points), with help (1 point), on my own with difficulty (2 points), and on my own (3 points)) response options. A higher total score will indicate greater independence [63].

Upper extremity function

*9-Hole Peg Test* will be used to evaluate hand dexterity. The participant will be asked to pick pegs one by one from the container and place them into the holes on the board as quickly as possible. Participants must then remove the pegs one by one and replace them back into the container. The time taken to complete this procedure will be recorded for each hand [64].

Balance

*Dynamic Gait Index* will evaluate the patient’s ability to maintain balance while walking with different task demands in 8 dynamic conditions. Items will be rated on a 4-point Likert scale. The total score will range between 0 and 24 points, with higher scores denoting better performance [65].

Fatigue

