### Data analysis

Data will be entered and analyzed using SPSS version 13. Each participant will have a registration number. All printed questionnaires and datasets will be stored in a secure locker and computer, respectively. Missing data will be handled by random coefficient analysis [68]. Intention-to-treat analysis will be performed for dropout participants during treatment sessions or follow-up assessments. Dropout participants will not be excluded from the sample size and data analysis. There will be no planned interim analyses and no planned stopping rules for this trial. The mean (standard deviation) or median (inter-quartile range) will be calculated for quantitative variables. For categorical variables, frequency (percentages) will be used. To check the normality of data, Shapiro-Wilk, graphical methods, and numerical indices will be used.

Quantitative demographic variables between the three groups will be compared using one-way ANOVA or Kruskal-Wallis tests. Chi-squared will be used for comparing the categorical variables between the groups. If there will be no significant difference between various outcome measures in the three groups at baseline, outcome measures will be analyzed using a 3 × 5 repeated measure analysis of variance with group (occupation-based interventions with responsibility feedback; occupation-based interventions without responsibility feedback; conventional) as between-subject factor and time (baseline, session 9, session 17, post-intervention, follow-up) as within-subject factor. A Tukey post hoc test will be performed for multiple comparisons. However, if a significant difference will be obtained for outcome measures in the three groups at baseline, a separate regression analysis will be done by considering group and baseline as covariates at each assessment point (i.e., session 9, session 17, post-intervention (week 13), follow-up (week 25)). The differences will be calculated via Kruskal-Wallis. All analyses will be considered significant with a 2-tailed *P* < 0.05.

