## Discussion

This trial will be innovative with a novel aspect that could pave the way for future studies. Although previous studies [25, 26] have investigated the effect of individualized OT, some methodological issues (i.e., intensity and structure of intervention) impede drawing rigorous conclusions. Moreover, a recent systematic review indicated that these individualized OT interventions provide a low to moderate strength of evidence for improving IADL performance and participation [5].

In response to these issues, this high-intensity, structured, client-centered, and occupation-based trial will be conducted by utilizing the concept of responsibility. This intervention will be delivered with a home-based approach. Therefore, future studies can compare the cost-effectiveness of this intervention in relation to interventions implemented in outpatient settings. Findings from this proposed study are expected to expand the knowledge of clinicians and help them in evidence-based decision-making processes.

This study will have some limitations. First, intervention delivery may be disrupted due to weather and therapist or patient sickness. Available therapists within the team will be incorporated to cover sickness leaves. Second, the results can only be generalized to people with PD who receive home-based interventions. Third, patients may underestimate or over-report the outcomes of the trial due to the use of self-report measures for evaluation. Fourth, patients may experience “on/off” fluctuations during assessment sessions.

In conclusion, the results of this proposed trial may result in enhanced participation (i.e., the ultimate goal for both patients and therapists) that would benefit other motor and non-motor symptoms in people living with PD.

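### One two-tailed P < 0.05 rule covers at least 15 secondary outcomes, with no control across outcomes and no statement that secondary results are exploratory

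*Protocol article*

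**What the plan says.** The protocol article fixes a single primary outcome: "The primary outcome of this trial will be participation satisfaction", measured with USER-P. The Methods part of the Abstract then lists the secondary outcomes: "Participation frequency and restriction, self-perceived performance, performance satisfaction, motivation, volition, sense of agency, responsibility, physical activity, community integration", followed by "activities of daily living (ADL), instrumental ADL, upper extremity function, balance, fatigue, and quality of life will be measured as secondary outcome measures".

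The Data analysis section does not separate primary from secondary. If the arms do not differ significantly at baseline, "outcome measures will be analyzed using a 3 × 5 repeated measure analysis of variance", with group and time as factors. If they do differ, a separate regression is run at each of the four later assessments. Tukey's test is named for the post hoc comparisons. The section closes with "All analyses will be considered significant with a 2-tailed *P* < 0.05".

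The article gives no order of testing for the secondary outcomes, no adjustment across them, no condition that the primary result be significant first, and no statement that they are exploratory.

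**The concern.** The sentence on significance is a decision rule that the plan actually states, and it takes in every analysis. Anyone following it may call any secondary outcome significant at 0.05, whatever the primary outcome shows and however many others were tested. Across 15 or more outcomes, at least one chance finding becomes quite likely.

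The trial has 45 patients and was sized on the primary outcome alone. If the primary result were null, the plan as written would still allow an isolated secondary P value below 0.05 to be presented as a demonstrated difference between arms. What is at stake is how far secondary findings can be believed. The test of the primary outcome is not in question.

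**Working it through.** **Inputs from the protocol article**
- Significance level: 0.05, two-tailed, for all analyses (Data analysis).
- Secondary outcomes: the Abstract names 10 in the first part of its list (frequency, restriction, self-perceived performance, performance satisfaction, motivation, volition, agency, responsibility, physical activity, community integration) and 6 in the second (ADL, IADL, upper extremity function, balance, fatigue, quality of life), so 10 + 6 = 16. ADL and IADL share the Nottingham scale (Secondary outcome measures), which leaves at least 15.
- Design: three arms at 1:1:1, five assessments, 45 patients, correlation among repeated measures 0.25 (Trial design; Sample size calculation).

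**Assumption.** The documents give no correlation r between outcomes, so I show r from 0 to 0.7.

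**The plan's own figure.** The article states no error rate across outcomes. The figure it does give, the sample size, reproduces for the group-by-time interaction. With f = 0.25, N = 39, m = 5 assessments and within-person correlation 0.25, the noncentrality is f² × N × m / (1 − 0.25) = 0.0625 × 39 × 5 / 0.75 = 16.25, on 8 and 4 × (39 − 3) = 144 degrees of freedom. Power is 0.812; N = 36 gives 0.771. Then 39 × 1.15 = 44.85, hence 45. I therefore simulated 3 × 15 patients.

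**One test per outcome, independent outcomes**
- Expected false positives: 15 × 0.05 = 0.75.
- Chance of at least one: 1 − 0.95^15 = 0.537. With 16 outcomes: 1 − 0.95^16 = 0.560.
- Counting only one prespecified direction (0.025 per outcome): 1 − 0.975^15 = 0.316.

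**One test per outcome, correlated outcomes.** For equicorrelated normal statistics with c = 1.96, the chance is 1 − ∫ [Φ((c − √r·x)/√(1−r)) − Φ((−c − √r·x)/√(1−r))]^15 φ(x) dx. For one direction, the second Φ term is dropped.

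**Planned ANOVA.** The 3 × 5 analysis was simulated with no true effects: 15 outcomes, compound symmetry over time at 0.25, 4,000 replicates.

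| Chance of at least one false result over 15 outcomes | r = 0 | r = 0.3 | r = 0.5 | r = 0.7 |
|---|---|---|---|---|
| Either direction, normal formula | 53.7% | 45.7% | 36.1% | 25.6% |
| Group effect, simulated | 53.2% | 46.6% | 37.5% | 27.7% |
| Group-by-time, simulated | 53.8% | 47.6% | 38.0% | 28.8% |
| Group or group-by-time, simulated | 77.8% | 71.8% | 60.9% | 48.7% |
| One direction, normal formula | 31.6% | 23.5% | 18.1% | 12.8% |
| Tukey on group effect, only A>C, B>C or A>B, simulated | 33.2% | 25.6% | 21.5% | 16.1% |

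A second simulation of the same design gave 54.5%, 47.9%, 39.0% and 28.6% for group-by-time, and 77.6%, 72.5%, 61.9% and 47.4% for either test.

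The fourth row matters because the article does not say whether the group effect or the interaction decides. The fallback regressions at four assessments are left out of these figures and would add tests.

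**With control across outcomes.** A threshold of 0.05/15 = 0.0033 gives 1 − (1 − 0.05/15)^15 = 4.9% under independence. Simulated for the interaction, it gives 4.4%, 4.3%, 3.9% and 3.0% at r = 0, 0.3, 0.5 and 0.7.

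**The case against.** The other side has several good points.

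- **What an article may leave out.** A testing hierarchy or an exploratory label is commonly left to the analysis plan, which is not shown. By itself, its absence would be no finding. The point survives because the article states a rule for all analyses, which a later plan would have to override.
- **Unadjusted secondary outcomes are common practice.** Beside one clearly named primary outcome this is defensible, and the labels primary and secondary already signal different weight. I accept this, so mandatory correction is not the remedy. What is missing is a limit on what an unadjusted secondary P value may be used to claim.
- **No promised rate is broken.** The 5% in Data analysis is a level per analysis, and the 5% in Sample size calculation belongs to the primary outcome. The article nowhere claims 5% over the secondary family, so the figures above should not be read as multiples of a stated rate.
- **The Discussion does not plan secondary efficacy claims.** A reader might infer that it does from the remark that enhanced participation "would benefit other motor and non-motor symptoms in people living with PD". That sentence only says what the trial may lead to, as a consequence of better participation. I do not rely on it.
- **Subscales.** The motivation, community-integration, PDQ-39 and other component scores could enlarge the family, but the article describes how they are scored and does not say that each is tested. I count only 15.

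**Conclusion.** The point holds as a limit on secondary claims. As written, the plan permits unprotected significance claims across at least 15 secondary outcomes. With one test per outcome and no true effects, the chance of at least one false significant difference in either direction is about 54% under independence, about 36-39% at an assumed correlation of 0.5 and about 26-29% at 0.7. A false result in the hypothesised direction has a chance of about 16-33% under Tukey on the group effect, over the same range of correlations. If either the group or the group-by-time test can support a claim, the chance of any false significant difference is about 47-78%.

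A reader might infer that a false claim of benefit has a chance of 40% or more. The documents do not support that. With one test per outcome, 40% is not a floor: it is passed only up to a correlation of about 0.4. Those figures also count differences in either direction, including ones that favour conventional therapy. Nor does any of this inflate the error rate of the primary outcome, which keeps its own 5% level.

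The figures rest on equal correlation between outcomes, normal data and complete follow-up of 45 patients.

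**What to change.** In Data analysis, replace the blanket significance sentence with text to this effect: *The two-tailed 0.05 level applies to the confirmatory test of the primary outcome, USER-P satisfaction. All secondary outcomes are exploratory. They will be reported as estimates with 95% confidence intervals, not adjusted for multiplicity, and will not be taken as evidence of efficacy if the primary result is not significant.*

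Optionally, if the investigators want confirmatory secondary claims, they can test the secondary scores with Holm's procedure at a familywise 5%, and only after a significant primary result. The list of scores in that family would then need to be fixed in advance. With 15 scores, the smallest P value would be compared with 0.0033.

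The change costs a sentence or two, with no new data or patients. The small downside is that an isolated secondary P value below 0.05 can no longer be presented as a confirmed effect.

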## Discussion

This trial will be innovative with a novel aspect that could pave the way for future studies. Although previous studies [25, 26] have investigated the effect of individualized OT, some methodological issues (i.e., intensity and structure of intervention) impede drawing rigorous conclusions. Moreover, a recent systematic review indicated that these individualized OT interventions provide a low to moderate strength of evidence for improving IADL performance and participation [5].

In response to these issues, this high-intensity, structured, client-centered, and occupation-based trial will be conducted by utilizing the concept of responsibility. This intervention will be delivered with a home-based approach. Therefore, future studies can compare the cost-effectiveness of this intervention in relation to interventions implemented in outpatient settings. Findings from this proposed study are expected to expand the knowledge of clinicians and help them in evidence-based decision-making processes.

This study will have some limitations. First, intervention delivery may be disrupted due to weather and therapist or patient sickness. Available therapists within the team will be incorporated to cover sickness leaves. Second, the results can only be generalized to people with PD who receive home-based interventions. Third, patients may underestimate or over-report the outcomes of the trial due to the use of self-report measures for evaluation. Fourth, patients may experience “on/off” fluctuations during assessment sessions.

In conclusion, the results of this proposed trial may result in enhanced participation (i.e., the ultimate goal for both patients and therapists) that would benefit other motor and non-motor symptoms in people living with PD.

## Trial status

The conception of the occupations and responsibility feedback statements are finished. Recruitment started in September 2022. It is expected that assessments for the last included patients will be completed by June 2023. If any modifications will be needed in the protocol (including study design or procedures), it will be agreed upon by the Iranian Registry of Clinical Trials. The current protocol (Code: IRCT20140304016830N13) is version 1.0, dated 19 August 2022.

## Availability of data and materials

The datasets used and analyzed during the study will be available upon reasonable request from the corresponding author. Questionnaires and evaluation forms for each participant will be stored in a secure locker. A code will be assigned to each participant’s folder. Double data entry and range checks for data values will also be done to promote data quality.

## Abbreviations

PD: Parkinson’s disease
ADL: Activities of daily living
OT: Occupational therapy
MOHO: *Model of Human Occupation*
OTiP: Occupational Therapy in Parkinson’s Disease
LED: Levodopa equivalent dose
IADL: Instrumental activities of daily living
USER-P: Utrecht Scale for Evaluation of Rehabilitation-Participation
Phone-FITT: Phone Frequency, Intensity, Time, and Type
PDQ-39: Parkinson’s Disease Questionnaire
